## Abstract

**Background:**

Disturbances in bodily well-being represent one key source of suffering and impairment related to cancer. There is growing evidence that body psychotherapy (BPT) is efficacious for the treatment of various mental disorders. However, with regard to cancer patients, evidence is scarce. The aims of this project are to evaluate whether bodily disturbances in post-treatment cancer patients can be improved by group BPT, and to estimate the efficacy of intermittent smartphone-triggered bodily interventions.

**Methods:**

The project is a bi-center study with two participating centers in Switzerland, applying a pre-post convergent parallel design of a weekly group BPT using a waiting-period comparator, including a nested RCT during the group BPT phase. During the BPT phase, either a smartphone-triggered bodily intervention or a smartphone-triggered control intervention is provided at random over 5 consecutive weeks, on 6 days weekly. Patients who had received curatively intended treatment for any malignant neoplasm (treatment being completed ≥3 months) and are suffering from bodily disturbances are screened to assess eligibility. Sample size estimation is based on an a priori power analysis. We plan to include a total of *N* = 88 subjects, aiming at at least 52 completers.

Patients are surveyed three times (baseline assessment (T0), pre- (T1) and post-intervention assessment (T2)), and on a daily basis along BPT during five consecutive weeks. The primary outcome, bodily disturbances, is assessed using the ‘Body Image Scale‘(BIS). For the secondary outcomes standardized questionnaires are used to assess changes in experience of presence and vitality, mood, body mindfulness, somatic symptoms and somatic symptom disorder, quality of life, anxiety, and depression including suicidal tendency, vitality and mental health, as well as group cohesion. Using semi standardized interviews (at T0 and T2), we aim to explore the relation of BPT with bodily disturbances and body image in post-treatment cancer patients, as well as the acceptance and burden of the intervention.

**Discussion:**

The proposed study has strong potential benefits for cancer patients, as it may pave the way for new therapeutic approaches to treat bodily disturbances, which persist despite curative tumor therapy. These may considerably improve patients’ biopsychosocial well-being and quality of life.

**Trial registration:**

ClinicalTrials.gov
NCT03707548 (registered 9 October 2018; retrospectively registered).

## Background

Cancer is a major public health issue and related to a high burden of disease. With an increasing number of patients surviving cancer, the high individual cancer-related burden is of growing importance. As recently indicated by the Global Burden of Disease (GBD), this burden is not only caused by fear of mortality but also by physical and psychosocial impairment [1–3]. It is not only caused by the tumor and its treatment but also originates from cancer-related experiences and the suffering caused by the disease. Notably, cancer related burden may persist even if the neoplasm has been treated successfully [4–8].

Cancer-related impairments often go along with disturbances in bodily well-being [9–14]. However, bodily disturbances are multidimensional, and varying and sometimes conflicting definitions are used [9, 15–17]. When using the term in the context of our study, we refer to the definition of Rhoten. She identified key aspects of body image disturbances which include the self-perception of change in appearance and displeasure with this change, a decline concerning various aspects of physical functioning and the psychological distress caused by these changes [16].. Body image disturbances are highly prevalent in cancer patients [9, 18, 19] and may persist despite successful interventions that target the tumor itself. They pose a major challenge to the well-being and quality of life of cancer patients and require to be appropriately addressed by care providers.

There is some evidence that body psychotherapy (BPT), defined as ‘psychotherapeutic treatment of mental disease or suffering, concomitantly using bodily and mental psychotherapeutic means’ (see [20]) is efficacious for the treatment of various mental disorders [21–24]. However, with regard to cancer patients, evidence of BPT is scarce [25, 26]. BPT explicitly targets bodily aspects, such as perceptions, feelings, and attitudes towards the body, which are of paramount importance in the context of bodily disturbances in cancer patients. Therefore, scrutinizing BPT as an intervention to reduce disturbances of bodily well-being appears to be highly promising. It may offer possibilities to directly aim at treatable mechanisms, which are the cause of cancer-related disturbances in bodily well-being. These reflections are in line with the recently suggested focus on an ‘experimental therapeutic approach’ of the National Institute of Mental Health as one of the most prominent funding institutions in this field [27].

Our study aims at evaluating the potential of body psychotherapy (BPT) to address cancer-related bodily disturbances. The thereby applied intervention *‘group body psychotherapy for post-treatment cancer patients’* is based on BPT as an experience-oriented approach [20, 28, 29]. The overall goal of this group BPT is to relieve bodily disturbances, caused or triggered by the preceding cancer and related treatments. Thus, the group BPT should support patients to learn how to cope with undesirable bodily sensations, feelings, and disturbances, such as changes in overt body image [30, 31] as well as changes in attitudes towards and perceptions of their own body [32]. This includes feelings of insecurity and vulnerability [33–35], of being stigmatized [10], of impaired functioning [35, 36], as well as feelings of disconnectedness from one’s own body [34].

### Study aims and objectives

The aims of this trial are to evaluate whether bodily disturbances in post-treatment cancer patients can be improved by group BPT, and to estimate the efficacy of intermittent smartphone-triggered bodily interventions (German acronym ‘KPTK: **K**örper**p**sycho**t**herapie bei **K**rebs’ in English: BPT for cancer patients. For trial registration data see Additional file 1). We assume that bodily disturbances will improve from pre- to post-BPT in post-treatment cancer patients. Furthermore, participants will show better immediate outcomes with regard to mood and bodily well-being if they receive smartphone-triggered bodily interventions as compared to smartphone-triggered control interventions. With this non-randomized evaluation of a weekly group BPT using a waiting-period comparator, with a nested randomized controlled trial (RCT) we will primarily obtain information on the efficacy of the intervention. Furthermore, we will be able to investigate intervention effects and mechanisms of action in more detail, together with acceptance and perception of the intervention, unwanted effects and burden to patients.

The primary objective of the planned project is to evaluate whether group BPT is related to reduction of bodily disturbances in post-treatment cancer patients.

Secondary objectives of the project are
to assess if BPT is related to more body awareness/mindfulness;to estimate, whether intermittent smartphone-triggered bodily interventions go along with immediate improvements in bodily well-beingto evaluate, whether BPT is related to improvements in mental well-being (anxiety, depression, somatization, pain, etc.) and quality of life;to assess group processes/cohesion;to assess aspects of the intervention, such as
recruitment and inclusion;undesired side effects (‘safety assessment’);from the patients’ perspectives:
(i)acceptance and burden of the intervention (this assessment is recommended according to recent initiatives, such as ‘Partnering with Patients’ launched by the British Medical Journal (BMJ) [37]);(ii)suggestions for improvement of the intervention.

## Methods/design

In this non-randomized evaluation of a weekly group BPT with a nested RCT (smartphone-triggered bodily interventions during group BPT) participants first undergo a waiting period (duration if possible 6 weeks; given that recruitment for a group intervention is difficult, reasonable exceptions of a shorter waiting period are allowed) followed by the group BPT (6 weekly sessions, 90 min each). During the group BPT, either a smartphone-triggered bodily intervention or a smartphone-triggered control intervention is provided at random (randomization on a daily basis) over a period of 5 consecutive weeks on 6 days per week. The project is based on a convergent parallel design. We apply quantitative and qualitative assessments, as described in more detail below. We depict the outline of the study design and the flow of study participants in Fig. 1.

**Fig. 1 Fig1:**
[figure not shown]
Outline of design and participant flow of the study

Following recommendations from the BMJ to improve patient involvement in research [37] we involved two patients, who had participated in the first conducted BPT group [25] beyond the study descript here, in the translation process of the BIS and the development of semi-standardized questionnaires, as well as in the preparation of the study information. Furthermore, both were asked to report on their experiences, and to review the planned trial and the study materials regarding their practical applicability and acceptance. When reporting the study, we took into account the guidelines and recommendations of the Consolidated Standards of Reporting Trials (CONSORT) and Transparent Reporting of Evaluations with Non-randomized Designs (TREND) statements [38, 39] and we adhered the guidelines for Standard Protocol Items: Recommendations for Interventional Trials (SPIRIT), see Additional file 2 [40].

### Study sample

We intend to include a total of 88 patients (44 at each study side). With an expected response rate of approximately 70%, we aim at a sample size of 52 completers (26 per participating center). The therapeutic intervention provided in this study aims at post-treatment cancer patients suffering from disturbances in bodily well-being. Patients having received curatively intended treatment for malignant neoplasms at the participating institutions, are screened according to the eligibility and exclusion criteria outlined in Table 1.

**Table 1 Tab1:** Inclusion and exclusion criteria

*Inclusion criteria:*	
• Having received curatively intended treatment for any malignant neoplasm;	
• Primary treatment (surgery, radiotherapy, chemotherapy) being completed ≥3 months ago before study inclusion. Any other ongoing anti-tumor therapy is allowed (e.g., hormonal therapy, adjuvant immunotherapy);	
• Bodily disturbances (BIS ≥10) (= clinical cutoff for body image dissatisfaction [9]); OR ((BIS = 2–9) AND ((patient-assessed distress due to bodily changes (VAS-B; 0–10) ≥ 5) OR (therapist-assessed awareness of bodily changes (VAS-A) ≥ 5 AND therapist-assessed related distress due to bodily changes (VAS-B, 0–10) ≥ 5)))	
• No sign of progress or recurrence of malignancy at study inclusion according to treating physician;	
• Score of 0 or 1 according to the PS of the ECOG [41];	
• Having an anticipated life expectancy of ≥12 months, according to treating physician (recent evidence suggests that this is the best source for prediction of survival [42]);	
• Age 18 years or older;	
• Capacity to participate in group BPT sessions in Basel or Winterthur, 3 study assessments, and the smartphone-triggered interventions;	
• Ability to provide informed consent.	
*Exclusion criteria:*	
• Suffering from a severe current mental disorder;	
• Risk of current suicidality, as indicated by a suicide item score ≥ 2 in the BDI-II [43], as this group BPT intervention is not appropriate to support suicidal patients in acute crises. (Given a score ≥ 2, need for support will be assessed and if required, patients are instructed to call for or transferred to local psychiatric support);	
• Participation in any other clinical trial with a psychosocial intervention;	
• Receiving any other current psychotherapeutic treatment with the exception of already existing long-lasting therapies (≥ 6 months);	
• Inability to understand and speak German.	

*Abbreviations*: *BDI* Beck Depression Inventory, *BPT* Body psychotherapy, *ECOG* Eastern Cooperative Oncology Group, *PS* Performance score, *VAS* Visual analog scale

### Recruitment and screening

Recruitment takes place at University Hospital Basel and at the Cantonal Hospital Winterthur. Further, potential participants are approached via public advertisements (e.g. advertisement in public transport and on the website of the Basel Cancer League). Patients having received curatively intended treatment for any malignant neoplasm (treatment being completed ≥3 months) and suffering from bodily disturbances due to the cancer diagnosis and treatment are provided with oral and written information about the study and asked if they are willing to participate. Patients are informed by trained research nurses or the project leader. In addition, the date and time of the specific BPT group are clarified with each participant in advance. Once written informed consent has been obtained, patients are screened with baseline assessment (T0), including standardized questionnaires and a semi-structured baseline interview whether they are eligible for the BPT intervention or not. Non-eligible patients are provided with information regarding alternative therapeutic support. Included patients undergo a waiting period of 6 weeks (given that recruitment for a group intervention is difficult, reasonable exceptions of a shorter waiting period are allowed) followed by the pre-intervention assessment (T1), weekly assessments after each group BPT session, and daily pre−/post smartphone-triggered assessments. After completion of the group BPT phase, the post-intervention assessment (T2) with standardized questionnaires and a semi-structured post-intervention interview takes place (Table 3 gives an overview of assessment instruments and time points).

### Withdrawal and discontinuation

Study participation is voluntary and can be withdrawn at any time during the study. If patients withdraw consent to participate in the study due to of any personal reasons, they will not be excluded from participation in group BPT. An investigator may terminate participation in the study if any clinical adverse events or medical situations occur and the continued participation in the study would not be in the best interest of the participant. Participation may also be terminated if the participant meets an exclusion criterion (either newly developed or previously not recognized) that does not allow further study participation. Thus, according to the “Withdrawal of Subjects from Research Guidance” [47], already collected data that is related to any participant who chooses to withdraw from the study will be retained and analyzed. We will anonymize these data after data evaluation has been completed.

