### Statistical and content analyses

Descriptive analyses of continuous variables will include the calculation of central tendency and dispersion; descriptive analyses of categorical variables will include numbers and frequencies.

We intend to use inferential statistics to compare outcomes and parameters over time: (1) from baseline to post group BPT intervention and (2) from pre to post smartphone-triggered bodily intervention. We intend to compare changes from T1 to T2 with changes from T0 to T1. Therefore, we intend to use mixed effect generalized linear models, which will also be used to assess potential mediators of therapeutic changes. Baseline equivalence between T0 and T1 will be assessed in order to adjust potential baseline differences and that way to reduce potential bias arising from the nonrandomized study design. We intend to conduct additional analyses, including adjusted (e.g., age, gender) and subgroup analyses (e.g., cancer entity, BPT group composition, level of somatic distress). All statistical tests will be two-sided, and *p*-values ≤0.05 will be considered statistically significant. In the event of multiple comparisons, Bonferroni-Holm corrections will be carried out.

We intend to analyze qualitative data based on thematic analyses, aiming at identifying themes within the data and at establishing meaningful categories, their interrelation, and their relation to the outcomes of the intervention [68, 70].

Intention-to-treat analyses will include all patients being enrolled in the study and randomized. Per protocol analyses will follow an all-patients-receiving-intervention perspective. Whenever appropriate, we are going to use multiple imputation methods [71].

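### The protocol lets the investigator end study participation on grounds that can reflect deterioration and provides for no outcome assessment afterwards, so T2 data can be missing informatively.

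*Protocol article*

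**What the plan says.** The section Withdrawal and discontinuation of the protocol article gives two routes by which the investigator can end participation in the study.

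- **Medical grounds:** "An investigator may terminate participation in the study if any clinical adverse events or medical situations occur", where continuing would not serve the participant's interest.
- **Exclusion criteria:** "Participation may also be terminated if the participant meets an exclusion criterion (either newly developed or previously not recognized"), restricted to a criterion "that does not allow further study participation".

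On data, the section says that "already collected data that is related to any participant who chooses to withdraw from the study will be retained and analyzed". That sentence names people who choose to withdraw. It does not mention those whom the investigator takes out.

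Table 1 lists five exclusion criteria. Three of them are "Suffering from a severe current mental disorder", "Risk of current suicidality, as indicated by a suicide item score ≥ 2 in the BDI-II", and "Receiving any other current psychotherapeutic treatment with the exception of already existing long-lasting therapies" of at least 6 months. The other two are taking part in another psychosocial trial and not understanding or speaking German.

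T2 takes place after the group therapy phase is completed (Recruitment and screening). The analysis section plans an intention-to-treat analysis of all enrolled and randomized patients, mixed models comparing the T1 to T2 change with the T0 to T1 change, and this on missing data: "Whenever appropriate, we are going to use multiple imputation methods".

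**The concern.** The rule ends participation in the study, and the protocol does not describe the intermediate state in which a person stops the therapy but still gives outcomes. It separates study and treatment in the opposite direction only: someone who withdraws study consent may stay in the therapy group.

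Several grounds for termination can mark a person who is getting worse. If such a person leaves during the therapy phase, the T2 BIS is missing for a reason connected with how that person was doing. The primary question is answered within one group, before and after therapy. No parallel arm suffers the same losses, so selective loss of poor T2 scores is not offset by design. The nested randomization allocates days within a person and cannot help here.

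Unwanted effects are a stated objective, and Table 3 schedules the safety questions only in the T2 interview. A terminated participant could miss the one planned interview on the subject.

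**Working it through.** **The plan's own figures.** The inputs from Sample size estimation are 52 completers, d = 0.5 and stated power 0.94; two-sided testing at 0.05 is from the analysis section. A paired t test has noncentrality 0.5 × √52 = 3.61 on 51 degrees of freedom and power 0.943, which agrees. Enrolment also reproduces if the 30% dropout and the 10% margin are added: 26 / (1 − 0.40) = 43.3, so 44 per site and 88 in total. The present point changes neither figure. The 30% covers all dropout, and no rate is given for termination by the investigator.

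**Where T2 can be lost.** Four statements, read together:

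1. Termination is from the study (Withdrawal and discontinuation).
2. T2 follows completion of the therapy phase (Recruitment and screening), and nothing says it is sought from someone terminated earlier.
3. The weekly BIS is taken after group sessions (Assessments), so it stops when attendance stops.
4. The intention-to-treat set nevertheless includes all enrolled and randomized patients (Statistical and content analyses).

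People removed under statement 1 therefore stay in the set in statement 4, and their T2 has to come from a model or from imputation.

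**Illustration of size.** This is for a simple T1 to T2 mean among those with T2, in SD units of change, with improvement positive. Let D be the true mean change in everyone, p the share terminated without T2, and w the mean change of those terminated. Then

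completer mean c = (D − p·w) / (1 − p), and bias = c − D = p·(D − w) / (1 − p).

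D = 0.5 is the protocol's planning effect. The values of p and w are assumptions.

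| p | c, w = −0.5 | bias | c, w = −1 | bias |
|---|---|---|---|---|
| 2% | 0.51/0.98 = 0.520 | 0.02 | 0.52/0.98 = 0.531 | 0.03 |
| 5% | 0.525/0.95 = 0.553 | 0.05 | 0.55/0.95 = 0.579 | 0.08 |
| 10% | 0.55/0.90 = 0.611 | 0.11 | 0.60/0.90 = 0.667 | 0.17 |

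If those terminated change as much as everyone else (w = D), the bias is zero.

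**Direction for the planned contrast.** The contrast is the T1 to T2 change against the T0 to T1 change. Someone who deteriorates and leaves during therapy keeps T0 and T1 and loses only T2, which pushes the contrast towards benefit. Someone who leaves during the waiting period can lose T1 as well, which also removes a poor result from the comparator period. The two effects can offset each other, so the net direction is not fixed.

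**The case against.** The strongest reply is that the documents do not say what a critical reader may infer from them. A reader might conclude that only data collected before termination are kept, that participants who worsen necessarily lose T2, and that the reported effect will therefore be inflated by a calculable amount. The text does not support this.

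- The rule is discretionary and covers only criteria incompatible with continuing.
- The retention sentence concerns voluntary withdrawal. What happens to follow-up after termination by the investigator is not stated.
- Not every criterion means worsening. Previously unrecognized criteria, another trial and language are not deterioration, new psychotherapy need not mean worse body image, and a worse BIS is not itself a criterion.
- The suicide item is scheduled only at T0, T1 and T2. A score that first crosses the threshold at T2 is found at the assessment that also yields the T2 BIS, and one found at T1 precedes the therapy.
- The planned analysis is not a completers-only mean. Mixed models using T0, T1 and weekly BIS, with imputation, reduce the bias if data are missing at random given the observed scores.
- Adverse events have their own notification route, and exclusions and dropout are recorded. Only the T2 interview is at risk, not all safety information.

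All of this stands, and it limits the point to a risk of unknown size. It does not remove the point. The protocol does not say which criteria rule out further participation, discretion can make removal depend on how the person is doing, and weekly BIS ends with attendance. Imputation is promised only where appropriate. The choice of imputation model and of sensitivity analyses belongs in the statistical analysis plan and is not criticized here.

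**Conclusion.** The point holds in limited form. The protocol states a rule that removes people from the study on grounds that can reflect deterioration, and it provides for no outcome assessment afterwards. This fits poorly with its own intention-to-treat set. T2 BIS and the T2 safety interview can therefore be missing informatively, and the T1 to T2 change can be biased towards benefit.

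For the planned contrast, neither size nor net direction can be derived from the documents. The tabulated figures apply only to a completers-only mean, and they assume that those terminated worsen by 0.5 to 1 SD against a true improvement of 0.5 SD. They show an order of magnitude and do not forecast this trial's result. The change is a cheap improvement and does not correct a demonstrated error. Whether the clinical stopping rule is right is not at issue.

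**What to change.** Add to Withdrawal and discontinuation that ending the intervention, or meeting an exclusion criterion after inclusion, does not by itself end outcome collection. Unless consent is withdrawn, seek the remaining questionnaires (at least the T2 BIS) and the safety questions at the time T2 was planned. Say that data from participants terminated by the investigator are retained and that these participants stay in the intention-to-treat analysis. Report terminations by reason and by phase (waiting period or therapy).

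The cost is a few sentences of protocol text, a few extra questionnaires, and a small burden for participants who have stopped. No clinical stopping decision changes.
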